##### Sample preparation for quality control analysis of serum, urine, and stool

Quality control (QC) samples served to monitor the repeatability and stability of the HPLC-MS system during multiple analyses of serum, stool, and urine. QC samples were injected six times initially and then randomly injected after every five unknown samples.

One sample of 20 μl was prepared for QC analysis and stored together with other aliquots.

Stool samples of 5 μl of final supernatant from each sample are pipetted and mixed.

After thawing on ice, each sample was vortexed for 30 s, and then all the samples were mixed, and acetonitrile was added (v/v ratio of 1:2 for serum, 1:1 for urine). The final mixed sample was centrifuged at 13,500 rpm for 10 min, and the liquid phase was transferred into a vial for LC-MS analysis.

#### Conditions for high-performance liquid chromatography mass spectrometry measurements

Metabolomic analysis was performed on Ultimate 3,000 HPLC System (Thermo Fisher Scientific, USA), coupled with a quadrupole TOF detector—TripleTOF 5,600 (AB Sciex, Canada), in both positive and negative (ESI+, ESI-) modes with the IDA method. Samples were analyzed *via* separation on a Phenomenex HPLC Kinetex C18 2.6 μm 150 mm × 3 mm column (Phenomenex, USA) with SecurityGuard Column ultra performance liquid chromatography (UPLC). The column temperature is maintained at a constant 35^°^C. The mobile phase is composed of A = 0.1% formic acid in water and B = 0.1% formic acid in 100% acetonitrile for both positive and negative modes; the linear elution gradient from 5% B (0–2 min) to 100% B (18–23 min) was applied; the initial gradient conditions were restored within 2 min (23–25 min), and the last 5 min of the HPLC method (25–30 min) were applied to maintain the beginning conditions. The flow rates were 250 μL min^–1^, and the sample injection volume was 5 μl. Samples were held in an autosampler at 4^°^C, and each sample was injected twice for each m/z range (50–500 Da, 500–1,200 Da). The electrospray ionization (ESI) source conditions were set as follows: ion source gas one (GS1) 35, ion source gas two (GS2) 30, curtain gas 25, ion spray voltage 4,000 V, and source temperature 450^°^C.

#### Chemicals and reagents

Chromatographic-grade methanol, acetonitrile, and acetic acid were purchased from Honeywell (Riedel-de-Haen) and Sigma Chemical. Ultra-high purity water was produced by the Milipore-Q water purification system ELGA Purelab Flex three (VWS Deutschland, Germany).

#### Plasma neurofilament light chain

Plasma neurofilament light chains (NfL) were determined with commercially available ultrasensitive single molecule array technology (Quanterix, Billerica, MA) by team-certified laboratory technicians blinded to clinical data.

#### Secondary outcome measures

##### Self-report and subjective measures

###### Depression and anxiety questionnaires

The second version of the Beck Depression and Anxiety Inventory (BDI-II, BAI) was also used. Each questionnaire consisted of 21 items rated by participants on a scale ranging between 0–3 points, i.e., a total score between 0–63 points; the more points, the more depression or anxiety (Beck et al., 1988, 1996).

###### Subjective feelings using visual analog scales

Participants expressed their feelings about different aspects during the past 2 weeks using seven visual analog scales (VAS) with a range of 0–10 points. The following questions were to be answered: VAS one—memory: How would you rate your memory in the past 2 weeks? (0 = bad memory; 10 = excellent memory); VAS two—digestion: What were your feelings during eating, after eating, digestion, and bowel movements in the past 2 weeks? (0 = total discontentment; 10 = total contentment); VAS three—How did you feel overall regarding your health during the past 2 weeks? (0 = very bad health; 10 = excellent health); VAS four—sleep: What was the quality of your sleep during the past 2 weeks? (0 = bad sleep quality; 10 = excellent sleep quality); VAS five—the feeling of anxiety: How anxious were you during the past 2 weeks? (0 = no anxiety; 10 = maximum anxiety); VAS six—tiredness: How physically tired did you feel during the past 2 weeks? (0 = not at all; 10 = maximum tiredness); VAS seven—pain: How much pain did you have during the last 2 weeks? (0 = no pain; 10 = maximum pain).

###### Additional questionnaires

A Questionnaire of Adverse Events (QAE) consisted of 22 questions with regard to possible negative events in the past 3 months. Participants chose dichotomized answers yes/no. A total score was a sum of yes answers ranging between 0 and 22 points.

A questionnaire regarding the side effects of probiotics contained 11 questions about possible side effects of probiotic use. Participants chose from a binary yes/no scale whether they had experienced a particular side-effect during the past 3 months. The following side-effects were monitored: nausea, vomiting, constipation, flatulence, bloatedness, stomach cramps, excessive thirst, headache, insomnia, allergic skin reaction (itchiness, redness), and infection (urinary tract infection, pulmonary infection, etc.).

The Dietary Habits Questionnaire contained 20 items or questions about the participants’ eating and drinking, digestion, and other dietary habits (e.g., How often do you consume different food groups? How often do you consume different types of drinks? How much do you drink per day? What is the frequency of your stool?). Participants had multiple answers to choose from.

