### Probiotics and placebo

Participants were offered to take one probiotic/placebo tablet each day along with two fiber/placebo fiber tablets. The time of tablet consumption was up to the participant. More details about the content of the probiotic and placebo tablets are available in Supplementary material 2. All the tablets were provided by the company NEXARS (Brno, Czech Republic).

Participants were asked about the adverse side effects of the intervention at the end of each 3 months using a structured list of hypothetical side effects.

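### The 11-item side-effect questionnaire asks about constipation but not diarrhoea or loose stools, so this instrument misses one direction of bowel-habit change

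*Protocol article*

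**What the plan says.** Under Probiotics and placebo, the article describes the product: "Participants were offered to take one probiotic/placebo tablet each day along with two fiber/placebo fiber tablets". The same section says how harms were elicited: "Participants were asked about the adverse side effects of the intervention at the end of each 3 months using a structured list".

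Under Additional questionnaires it gives the instrument. "A questionnaire regarding the side effects of probiotics contained 11 questions about possible side effects of probiotic use". The response format is closed: "Participants chose from a binary yes/no scale whether they had experienced a particular side-effect during the past 3 months". The content is then named: "The following side-effects were monitored: nausea, vomiting, constipation, flatulence, bloatedness, stomach cramps, excessive thirst, headache, insomnia, allergic skin reaction" (with itchiness and redness as examples), "and infection (urinary tract infection, pulmonary infection, etc".

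Three other instruments come near the topic:
- **Questionnaire of Adverse Events.** It has 22 yes/no questions about the past 3 months and is scored as a sum. The items are not shown.
- **Dietary Habits Questionnaire.** It has 20 items, some of them on digestion. Four examples are printed, one of which is "What is the frequency of your stool".
- **Second visual analogue scale.** It gives one 0–10 contentment rating over the past 2 weeks, covering eating, digestion and bowel movements together.

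**The concern.** A change in bowel habit can go either way. The questionnaire already treats gut effects as possible, since it asks about constipation, flatulence, bloatedness and cramps. It is therefore lopsided on its own terms: a participant whose stools became hard has a box to tick, and one whose stools became loose does not.

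What is at stake is the reading of the side-effect results. A table built from this questionnaire would have no row for diarrhoea, and a reader could take the missing row as evidence of good tolerability. Efficacy results are not affected.

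**Working it through.** No sample-size or power formula applies. The check is a count of items, followed by a comparison of the instruments.

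**1. Is the printed list complete?**
Stated number of questions: 11.
Named items: nausea (1), vomiting (2), constipation (3), flatulence (4), bloatedness (5), stomach cramps (6), excessive thirst (7), headache (8), insomnia (9), allergic skin reaction (10), infection (11).
Count: 11, equal to the stated 11. The omission cannot be put down to a shortened list.

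**2. Could the open ending of the list cover it?**
The abbreviation for further examples sits inside the brackets of the infection item. It widens the kinds of infection and adds no bowel symptom. A participant with an intestinal infection might tick that box, but the answer would not record diarrhoea.

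**3. What does the list cover?**
- Gut-related items: 6 of 11 (items 1 to 6).
- Items on constipation: 1 of 11.
- Items on diarrhoea or loose stools: 0 of 11. The symptom is not named anywhere in the article.

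**4. Do the other instruments fill the gap?**

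| Instrument | What is shown | What it can say about loose stools |
|---|---|---|
| Digestion visual analogue scale | One score for several feelings, 2-week recall | Indirect. It does not identify the symptom or its direction. It covers about 2 of 13 weeks (2/13 ≈ 15%) of a 3-month period. |
| Dietary Habits Questionnaire | 4 examples from 20 items, including stool frequency | Indirect. Frequency is not consistency. If each example is one item, 20 − 4 = 16 items are unseen. |
| Questionnaire of Adverse Events | 22 questions, none printed, sum score | Unknown. A relevant item cannot be ruled out, but the sum score alone would not display it. |

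**5. What is left unmeasured?**
The documents give no diarrhoea rate. Under assumed true rates of 5%, 10% and 20% in a period, the expected number affected among 91 participants is:
- 91 × 0.05 = 4.6
- 91 × 0.10 = 9.1
- 91 × 0.20 = 18.2

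None of these people would have an item to tick on this questionnaire. The rates are illustrative and are not estimates for this product.

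**6. What can be recovered from completed visits?**
Table 1 lists the Dietary Habits Questionnaire for all visits, and Trial design places the self-report measures at the first visit. A T1 stool-frequency answer should therefore exist. Proposed analysis says self-report outcomes were collected in person from everyone and pooled, so the 19 online participants and the 72 in-person participants (19 + 72 = 91) can both contribute. Trial design also says that no washout separates the two treatments. Group A's placebo period follows directly on probiotics, so T1 to T3 is the cleaner contrast.

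**The case against.** The strongest reply is that the gap belongs to one questionnaire and not to the trial. The Questionnaire of Adverse Events is a separate instrument with 22 unseen questions, and most Dietary Habits items are also unseen. The digestion scale asks about bowel movements directly and is a secondary outcome. The article is condensed and sends visit details to a supplement that is not shown, so open or spontaneous reporting may exist. All of this stands, and it limits the claim to the 11-item list.

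A reader might infer more, in four ways that the documents do not support:
- **That the trial would report 0% diarrhoea in both periods.** A symptom that is not asked about is unmeasured, and no rate follows for it.
- **That there was no open question at all.** The article describes none, but silence in a condensed article does not establish that.
- **That the side-effect comparison is biased toward safety.** The same list is used in both periods, so no bias is shown for the 11 listed symptoms. The article states no safety hypothesis and draws no tolerability conclusion.
- **That unseen bowel changes unblinded participants.** Nothing in the article links bowel symptoms to guessing the allocation.

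The reply does not remove the central fact. The list is complete as printed, and it is the instrument named for the side effects of the product. None of the other instruments is described as recording diarrhoea.

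**Conclusion.** The point holds for the dedicated side-effect questionnaire: 11 of 11 items are accounted for, one asks about constipation and none about diarrhoea or loose stools. Followed as written, this instrument cannot capture that symptom at any true rate. It is not established that the whole harm record lacks it.

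The verdict rests on two things: the article's count and list being accurate, and a judgement that loose stools are foreseeable with a probiotic and fibre product. The second is a reviewer's judgement, supported by the gut symptoms already on the list. The severity is minor, because the primary outcomes and the power figures are unaffected. The consequence is a limit on what can be said about tolerability.

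**What to change.** **Where the questionnaire is still used:** add one yes/no item on diarrhoea or loose stools, which makes 12 named items. Add an open item for any other complaint if none exists. The cost is one or two lines and no extra visit.

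**For visits already completed** (the article gives January 2021 to May 2022 as the study period):
1. Tabulate increases and decreases in the stool-frequency answer from T1 by treatment group. Rely mainly on T1 to T3, and show later visits as supportive only because there was no washout.
2. Check the full item lists of the Questionnaire of Adverse Events and the Dietary Habits Questionnaire. Report any relevant bowel item individually, in addition to any total score.
3. State that the tolerability conclusion covers only the symptoms asked about.

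This costs one extra table from data already collected and one sentence in the report. The downside is that stool frequency is an imperfect proxy for loose stools, and its answer categories are not shown. The table can flag a signal but cannot exclude one.

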##### Measures of personal characteristics and physical fitness

Participants’ physical fitness was evaluated using the Beurer BF 950 diagnostic scale and a series of physical prowess tests. The scale provided these personal characteristics: weight, body mass index (BMI), body water percentage, muscle mass percentage, and bone weight.

Additionally, participants were asked about their past and current physical activities and their frequency. They completed three tests of physical performance. Firstly, we counted how many times participants fitted up one dumbbell of one kilogram from the extended arm to their shoulder in 30 s. Secondly, we measured the time it took them to walk a specific distance of 2 × 17 m in the corridor there and back. Thirdly, we counted how many times they stood up from a sitting position in a chair and back in 30 s.

## Proposed analysis

Data on the cognitive outcomes of the participants will be analyzed separately for groups evaluated in person and online. The results of online participants were exploratory due to the low sample size. Biochemical, self-report, and physical fitness outcomes were collected in person for all participants and were analyzed together. Statistical analyses will be conducted using R or Statistica.

Descriptive statistics will be calculated for primary and secondary outcomes at each visit.

The analysis will proceed using a between-subjects unpaired *t*-test at each time point or using a within-subjects paired *t*-test to compare results between time points.

Additionally, we will include apolipoprotein E allele status and its influence on outcomes.

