##### Brief cognitive tests

Brief cognitive tests included the Clock Drawing Test (CDT), our newly developed the ALBA test, and a short cognitive battery (ABACO). The CDT was evaluated using our developed and validated scoring system called BaJa. It was weighted in favor of assessing clock hands and suppressing the contribution of the clock itself. It ranged from 0 to 5 points. The time of 23:20 was chosen as it is cognitively more difficult than 11:10 or 5:40, as proven in our report (Bartos et al., 2016). The CDT was used without modification in all testing sessions. The CDT was omitted in online testing.

The ALBA test is a newly developed three-minute examination of intentional and incidental short-term memory, which could differentiate patients with mild cognitive deficits from cognitively normal individuals. The innovative test paradigm was based on a recall combination of one short six-word sentence and six gestures. First, a participant was asked to remember a sentence. The following distraction included a demonstration of six gestures and their incidental and immediate recall. The final task was sentence recall (Bartos, 2019). Two alternate forms of the ALBA test are available with good comparable psychometric properties in the Czech Republic (Bartos and Diondet, 2020). Online ALBA was the same as the in-person one (Polanska and Bartos, 2022). A completed example of an ALBA form with detailed administration and evaluation instructions is shown in Supplementary Figure 1. The ALBA educational video is freely available at: https://www.youtube.com/watch?v=LyCuWc0-Gro.

Our in-house cognitive battery, ABACO, consists of five brief tests: (1) the Reading Encrypted Sentences subtest, (2) the sentence learning and recall, (3) verbal fluency test, (4) the PICture Naming and Immediate Recall (PICNIR), whose educational video is freely available at https://www.youtube.com/watch?v=cbJGtPG-nVA, and (5) the Five or Four-line test. Detailed information about them is in Supplementary material 3.

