##### A comprehensive battery of neuropsychological tests

The Rey Auditory Verbal Learning Test (RAVLT) is intended for verbal memory evaluation. The test includes immediate verbal memory (A1), learning performance as a sum of five trials (A1–A5), proactive interference (B1), retroactive interference (A5–A6), and loss after consolidation (A6–A7) (Bean, 2011). In the Czech Republic, there are three alternative versions of RAVLT to eliminate the practice effect due to retest (Preiss et al., 2012). In the current study, we used them in version order: one at T1, two at T3, three at T4, and one at T5 (Figure 2). Online RAVLT testing was the same as that done in person.

The Trail Making Test (TMT) included parts A and B. Part A was used to evaluate processing speed, attention, and visuospatial ability. Part B, in addition to the mentioned functions, also assessed mental flexibility as a part of executive functions (Oosterman et al., 2010; Preiss et al., 2012). As there was no alternate form of the TMT in the Czech Republic, we used the same form for each test. The TMT was replaced with phonemic verbal fluency tests starting with the letters NKP during the online testing.

The Digit Symbol subtest from the Wechsler Adult Intelligence Scale III (WAIS-III) assessed the processing speed (Kaufman and Lichtenberger, 2005; Preiss et al., 2012).

Category (animal) fluency tests in person and online and phonemic fluency tests with initial letters NKP during online testing were used to evaluate executive functioning, language, and semantic memory (Lezak et al., 2012). Each verbal test took 1 min.

Online testing also included the Digit Span subtest from WAIS-III, which measured short-term verbal and working memory capacity (Preiss et al., 2012).

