### Power calculation

Given our sample size, we will able to detect the effect size of Cohen’s d = 0.43 in the matched-pairs two-tailed *t*-test, assuming power = 0.8 and α = 0.05. This will be d = 0.51 in those tests when only in-person data could be used.

For between-group comparisons, we could detect the effect size of Cohen’s d = 0.59 in a two-sample two-tailed *t*-test, assuming power = 0.8 and α = 0.05. This would be d = 0.67, assuming the use of only in-person data.

All power calculations were performed in G*Power 3.1.9.7 Software (Faul et al., 2007). As we did not attain equal group numbers, the sensitivity of the matched-pairs *t*-test is computed for the smaller group. This means we could detect a slightly smaller effect size for larger groups than reported here.

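### RAVLT and ALBA are analysed separately by mode although described as the same online, so their main analysis rests on 72 of 91 participants, and it is unclear which detectable effect applies

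*Protocol article*

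**What the plan says.** The Proposed analysis section of the protocol article states: "Data on the cognitive outcomes of the participants will be analyzed separately for groups evaluated in person and online". It calls the online results exploratory and gives low sample size as the reason. Biochemical, self-report and fitness outcomes are analysed on everyone together.

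For two key memory tests the article describes no difference between modes. On the RAVLT: "Online RAVLT testing was the same as that done in person". On the ALBA: "Online ALBA was the same as the in-person one". Table 1 marks only the Clock Drawing Test (CDT), the Trail Making Test (TMT) and Digit Symbol as not given online. Animal fluency, RAVLT A7 and the ABACO battery appear in both modes.

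The Power calculation section gives two pairs of detectable effects, "assuming power = 0.8 and α = 0.05":
- Paired, all participants: "we will able to detect the effect size of Cohen’s d = 0.43 in the matched-pairs two-tailed" test. In-person data only: "This will be d = 0.51 in those tests when only in-person data could be used".
- Between groups, all participants: "we could detect the effect size of Cohen’s d = 0.59 in a two-sample two-tailed" test. In-person data only: "This would be d = 0.67, assuming the use of only in-person data".

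**The concern.** A small online group is a good reason not to rely on 19 people analysed alone. It is not a reason to leave them out of a combined analysis of a test they took in the same form. Splitting by mode is what makes the online sample small. As planned, the memory question in a memory trial is answered mainly on 72 participants.

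The two sections also fit together poorly. The Power calculation ties the weaker paired figure to the tests for which in-person data alone are usable. That reads naturally as CDT, TMT and Digit Symbol, leaving 0.59/0.43 for RAVLT and ALBA. The Proposed analysis makes every cognitive test in-person only for the main result. A reader cannot tell which figure applies to the memory outcomes.

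**Working it through.** **Inputs.** N = 91, of whom 19 online and 72 in person (Participant recruitment and allocation; Trial design). Two-sided α = 0.05 and power 0.80 (Power calculation). The paired test is computed on the smaller group, as that section says. The text does not state the sizes of the two sequence groups.

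**Formulas (noncentral t).**
- Two-sample: k = n₁n₂/(n₁+n₂), δ = d√k, df = n₁+n₂−2.
- Paired: δ = d√n, df = n−1.
- Stratified by mode: k = sum over modes of n₁n₂/(n₁+n₂), df = 91−3 = 88.
- Power = P(T(df, δ) > t(0.975, df)), solved for d at 0.80.

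**Step 1: reproduce the stated figures.**

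| Analysis | n | Computed d | Stated d |
|---|---|---|---|
| Between, all | 45/46 or 44/47 | 0.594 | 0.59 |
| Between, in person | 32/40 | 0.674 | 0.67 |
| Paired, all | 44 or 45 | 0.432 or 0.427 | 0.43 |
| Paired, in person | 32 | 0.511 | 0.51 |

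All four reproduce. The paired figures also reveal the splits. Only n = 32 rounds to 0.51 (31 gives 0.520, 33 gives 0.503). For 91, the smaller group must be 44 or 45 (43 gives 0.437). The inferred splits are therefore 32/40 in person and 44/47 or 45/46 overall, which leaves 12/7, 13/6, 14/5 or 15/4 online.

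**Step 2: can 72 reach the all-participant figures?** The best split, 36/36, gives 0.670 between groups and 0.480 paired in a group of 36. So no split of 72 reaches 0.59, or 0.43 on the plan's smaller-group basis.

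**Step 3: the online group alone.** Its most favourable split, 9/10, detects only d of about 1.37; 12/7 gives 1.41.

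**Step 4: combine the modes, stratified.** In person, k = 32×40/72 = 17.78.

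| Online split (inferred) | Online k | Total k | Detectable d | Power at d = 0.59 |
|---|---|---|---|---|
| 12/7 | 4.42 | 22.20 | 0.601 | 0.785 |
| 13/6 | 4.11 | 21.88 | 0.606 | 0.779 |
| 14/5 | 3.68 | 21.46 | 0.611 | 0.771 |
| 15/4 | 3.16 | 20.94 | 0.619 | 0.761 |
| In person only (32/40) | – | 17.78 | 0.674 | 0.689 |

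Simple pooling of all 91 gives power of about 0.79 at d = 0.59. In the paired test, a mode effect that is constant over visits cancels within each person. Moving from n = 32 to 44 or 45 raises power at d = 0.43 from 0.65 to 0.80–0.81.

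**Step 5: which tests qualify?** The article calls only RAVLT and ALBA the same in both modes. Table 1 puts animal fluency before RAVLT A1–A6 in person (3, then 4) and after it online (RAVLT 2, fluency 3). It puts RAVLT A7 before ABACO in person (13, then 14) and after it online (ABACO 5, A7 7). Animal fluency and A7 are therefore weaker candidates for combining.

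**The case against.** Separate analysis by mode is declared in advance, is conservative, and belongs to a study that describes its approach as explorative. Setting, battery and test order do differ between modes. This stands: the separation is a defensible choice that loses efficiency, not an error.

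Several stronger readings are tempting, and the documents do not support them:
- *The power statement is wrong or hides the loss.* The in-person figures are printed beside the others and reproduce.
- *The online data are thrown away.* Their cognitive data are analysed as exploratory, and these participants stay in all other outcomes.
- *The figures 0.59/0.43 apply to no primary outcome.* Biological markers, GDS and FAQ-CZ are listed as primary, and these groups of outcomes are analysed on everyone.
- *Combining restores the groups as matched.* The Trial design section says the 19 were removed from their original allocation, and the Abstract says online participants were randomly allocated to subgroups. Matching is a separate issue.
- *Combining fully recovers 0.59.* With stratification and the inferred splits it falls slightly short.

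Two further cautions stand. The timing of the switch to online is not given. The account of allocation, with testing at T1 before tablets at T2, implies that mode was fixed before treatment but does not say so. And 19 people can test only weakly whether the treatment effect differs by mode. Finally, d = 0.59 is a sensitivity threshold, not a hypothesised effect; it serves here only as a common yardstick.

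**Conclusion.** The point holds as an avoidable loss of precision and an unclear power statement. For RAVLT A1–A5 and ALBA, the planned main analysis sets aside 21% of participants for a reason that does not justify it. A mode-stratified analysis of all 91 would move the detectable between-group d from about 0.67 to about 0.60–0.62, and power at d = 0.59 from about 0.69 to about 0.76–0.79. These numbers rest on back-solved splits, a common treatment effect and variance across modes, and a mode fixed before treatment.

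Separately, the wording on detectable effects conflicts with the rule that separates all cognitive outcomes. One sentence can settle that, whichever analysis is kept.

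**What to change.** 1. For RAVLT A1–A5 and ALBA, add a combined analysis of all 91 stratified by mode (within-mode treatment contrasts combined, or mode as a covariate). Report the mode-specific results and a mode-by-treatment estimate beside it.
2. Keep CDT, TMT and Digit Symbol in person only. Use animal fluency and RAVLT A7 in combined form only as sensitivity analyses.
3. State which detectable d applies to each outcome. If modes stay separate, say that 0.67/0.51 governs all cognitive outcomes.
4. State when assessment mode was fixed relative to the start of tablets, and give the group sizes by mode.

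Cost: no new data. The between-group comparison becomes a simple stratified or linear model instead of a plain t-test. The added assumption of a common effect across modes can be checked only weakly, which is why the mode-specific results should stay in the report.
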